## 2.3 Benefit/Risk Assessment

KB109 is made from food-based monosaccharide sources, and it belongs to a class of commercially available compounds (non-digestible glucose-based carbohydrates) that have a

long history of safe use in food. The Sponsor has engaged an external scientific consulting organization that is frequently used by the food industry to prepare and make GRAS determinations. KB109 was concluded to be Generally Recognized as Safe (GRAS) for use in this study by experts recognized in the field to evaluate GRAS in accordance with the scientific requirements outlined in 21 CFR §170.30(b). This report is a sufficient basis for establishing the GRAS status of KB109 as intended for use as food in this study. FDA regulations recognize self-determination of GRAS status. Although tolerability varies among individuals and among nondigestible carbohydrates, the adverse effects of nondigestible carbohydrates are not qualitatively different from each other and are dose-dependent, quickly reversible, and localized to the GI tract ([Grabitske 2009](#)).

Kaleido's orally administered proprietary oligosaccharide mixture, KB109, holds promise in inducing a beneficial profile of SCFA production in the gut while driving the growth of commensal bacteria. Increased SCFA and the modulation in microbiome taxonomy may lead to a more appropriate immune and inflammatory response and may prevent an over-aggressive response, up to and including "cytokine storm" observed in patients with COVID-19. KB109 is determined to be GRAS its intended use in this study.

### **3 STUDY OBJECTIVES AND ENDPOINTS**

#### **3.1 Study Objectives**

##### **3.1.1 Primary Objective**

The primary objective of the study is to evaluate the safety of KB109 in addition to Supportive Self Care (SSC + KB109) compared to SSC alone in outpatients with mild-to-moderate COVID-19.

##### **3.1.2 Secondary Objective**

The secondary objective is to evaluate selected measures of health in outpatients with mild-to-moderate COVID-19.

##### **3.1.3 Exploratory Objectives**

The exploratory objectives are to evaluate:

- Measures of health in outpatients with mild-to-moderate COVID-19 during the follow-up period
- The changes in laboratory measures, specific biomarkers, serology and viral load in outpatients with mild-to-moderate COVID-19

## 3.2 Study Endpoints

### 3.2.1 Primary Endpoint

The primary endpoint is number of patients experiencing study product (SP)-related treatment-emergent adverse events (TEAEs).

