## **6.10 Randomization, Stratification and Blinding**

All patients deemed eligible for the study will be randomized in a 1:1 ratio to SSC + KB109 or SSC alone group using an interactive response technology (IRT) system. Randomization will be stratified by study site/center, age group ( $\geq 18$  to  $< 45$  years,  $\geq 45$  to  $< 65$  years,  $\geq 65$  years), and comorbidity status (Yes, No).

The study is an open-label study; therefore, no blinding is necessary.

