### 7.3 Causality

The PI or designee must make the assessment of relationship to SP for each AE. The PI or designee should decide whether, in his or her medical judgment, there is a reasonable possibility that the event may have been caused by the SP. If there is no valid reason for suggesting a relationship, then the AE should be classified as “not related”. Otherwise, if there is any valid reason, even if undetermined or untested, for suspecting a possible cause-and-effect relationship between the SP and the occurrence of the AE, then the AE should be considered “related”. The causality assessment must be documented in the source document.

The following additional guidance may be helpful:

- **Related (definitely, probably, possibly related):** The temporal relationship between the event and the administration of KB109 is compelling and/or follows a known or suspected response pattern to that product, and the event cannot be explained by the patient’s medical condition, other therapies, or accident.
- **Not Related (definitely not, unlikely related):** The event can be readily explained by other factors such as the patient’s underlying medical condition, concomitant

therapy, or accident and no plausible temporal or biologic relationship exists between the SP and the event.

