**Table 4 Half-width of the 95% CI for SP-related TEAE Rate**

| Evaluable Sample Size
(N/Group) | SP-Related TEAE
Rate | 95% CI  | Half-Width of the
95% CI |
|--------------------------------------------|---------------------------------|----------------|-------------------------------------|
| 148                                        | 10%                             | [5.8%, 16.2%]  | 5.2%                                |
|                                            | 20%                             | [14.1%, 27.7%] | 6.8%                                |
|                                            | 40%                             | [31.9%, 48.2%] | 8.2%                                |
|                                            | 60%                             | [51.8%, 68.1%] | 8.2%                                |
| 170                                        | 10%                             | [5.9%, 15.5%]  | 4.8%                                |

|  |     |                |      |
|--|-----|----------------|------|
|  | 20% | [14.3%, 26.8%] | 6.3% |
|  | 40% | [32.6%, 47.8%] | 7.6% |
|  | 60% | [52.2%, 67.4%] | 7.6% |

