## 8.3 Analysis Sets

### 8.3.1 Safety Analysis Set

The Safety Analysis Set will include all randomized patients. Patients will be included in the group based on the fact that whether or not they actually consumed any amount of KB109: patients who actually consumed any amount of KB109 will be in the SSC + KB109 group; otherwise patients will be in the SSC alone group.

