### 8.4.3 Analysis of Endpoints of Interest

#### Adverse Events (AEs)

The analysis of AEs will be based on the Safety Analysis Set. AEs will be coded using the most recent version of Medical Dictionary for Regulatory Activities (MedDRA).

A TEAE is defined as any AE starts or worsens in severity on or after the first dose of SP is taken for SSC + KB109 group or on or after the randomization for SSC group. Adverse event summary tables will include all TEAEs, SP-related TEAEs, SAEs, TEAEs by severity, and TEAEs leading to product discontinuation. Summaries will be presented by MedDRA system organ class and preferred term using frequency counts and percentages by group and overall.

The analysis of the following endpoints will be based on the Full Analysis Set unless otherwise specified.

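### The only primary endpoint, product-related TEAEs, cannot arise in the control group, so it does not answer the comparative primary safety objective

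*Protocol*

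**What the plan says.** Protocol Section 3.1.1 gives the primary objective as to "evaluate the safety of KB109 in addition to Supportive Self Care (SSC + KB109) compared to SSC alone". Section 3.2.1 and the synopsis attach a single endpoint to it: "The primary endpoint is number of patients experiencing study product (SP)-related treatment-emergent adverse events (TEAEs".

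Four other places decide what that endpoint can measure:

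- **Section 7.3 (Causality).** The investigator or a designee judges each event against the study product. The guidance for a related event includes that "The temporal relationship between the event and the administration of KB109 is compelling".
- **Section 6.10.** "The study is an open-label study; therefore, no blinding is necessary". The control group receives SSC only, with no placebo.
- **Section 8.3.1 (Safety Analysis Set).** Anyone who consumed any KB109 is analysed in the SSC + KB109 group; "otherwise patients will be in the SSC alone group".
- **Section 8.4.3 (Adverse Events).** A TEAE is one that starts or worsens "on or after the first dose of SP is taken for SSC + KB109 group or on or after the randomization for SSC group". Tables of all TEAEs, SP-related TEAEs, SAEs, TEAEs by severity and TEAEs leading to product discontinuation are planned by group. None apart from SP-related TEAEs corresponds to the primary endpoint.

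The precision statement in Section 8.1 is Table 4, titled "Half-width of the 95% CI for SP-related TEAE Rate". It takes one assumed rate per row (10%, 20%, 40%, 60%) at 148 and 170 evaluable patients per group.

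**The concern.** A comparative objective needs an endpoint that can occur in both groups. An event counted only if it is attributed to KB109 cannot properly be counted in patients who took none. The randomized control then adds nothing to the primary result, and background events from COVID-19, concomitant medicines or chance are removed by individual judgement instead of by comparison with the control group.

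That judgement is hard in this trial. GI disturbance and diarrhea are scored as COVID-19 symptoms (Section 4.3.4.1) and are also listed as expected effects of the product (Section 7.3.1). An investigator who knows the assignment must decide which they are, and the error could go in either direction. At stake is whether the headline safety result says anything about excess risk over SSC.

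**Working it through.** **1. Can the endpoint occur in the SSC group?** There are three routes, and none is valid.

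- A patient randomized to SSC who takes no KB109 has no administration to which an event could be related under Section 7.3.
- A patient randomized to SSC who does take KB109 is analysed in the KB109 group under Section 8.3.1.
- A patient randomized to KB109 who never takes it is analysed in the SSC group, but also has no exposure.

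Any related event recorded in the SSC group would be a misclassification. The count is zero by construction.

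**2. What does the primary result then show?** Two illustrations with assumed rates:

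| Assumed any-TEAE rate, KB109 | Assumed any-TEAE rate, SSC | True excess | Attributed to product | Primary result |
|---|---|---|---|---|
| 20% | 20% | 0 points | 10% | 10% v 0% |
| 40% | 20% | 20 points | 10% | 10% v 0% |

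The same primary result fits no excess and a 20-point excess. With SSC fixed at zero, the difference is just the KB109 rate. At 10% and 148 per group the Wald half-width is 1.96 × √(0.1 × 0.9/148) = 4.8 points, so the interval runs from 5.2 to 14.8 points and excludes zero in both rows.

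**3. Reproducing Table 4.** Evaluable numbers: 350 × 0.85 = 297.5, or 148.75 per group (shown as 148); 400 × 0.85 = 340, or 170 per group. Intervals: exact (Clopper-Pearson) for one proportion, with x = n × rate rounded, lower limit = 2.5% quantile of Beta(x, n − x + 1), upper limit = 97.5% quantile of Beta(x + 1, n − x).

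| n | x | 95% CI | Half-width |
|---|---|---|---|
| 148 | 15 | 5.8–16.2% | 5.2 |
| 148 | 30 | 14.1–27.7% | 6.8 |
| 148 | 59 | 31.9–48.2% | 8.2 |
| 148 | 89 | 51.8–68.1% | 8.2 |
| 170 | 17 | 5.9–15.5% | 4.8 |
| 170 | 34 | 14.3–26.8% | 6.3 |
| 170 | 68 | 32.6–47.8% | 7.6 |
| 170 | 102 | 52.2–67.4% | 7.6 |

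All eight rows agree with the printed table.

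**4. Precision for an endpoint that both arms can have.** For any TEAE, assuming the same rate p in both arms, the Wald half-width of the risk difference is 1.96 × √(2p(1 − p)/n). For example, at p = 0.2 and n = 148: 1.96 × √(0.32/148) = 9.1 points.

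| Assumed rate in both arms | 148 per group | 170 per group |
|---|---|---|
| 10% | 6.8 | 6.4 |
| 20% | 9.1 | 8.5 |
| 40% | 11.2 | 10.4 |
| 60% | 11.2 | 10.4 |

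The like-for-like (Wald) one-arm values at n = 148 are 4.8, 6.4, 7.9 and 7.9, so the ratio is √2, about 1.41.

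**5. Observation windows.** Under Section 8.4.3 the TEAE clock starts at first dose for KB109 and at randomization for SSC. Section 4.1 ships the kit overnight after randomization and starts Day 1 on the morning after receipt. If the kit leaves on the day of randomization (an assumption), the SSC window opens about two days earlier. This does not affect a count fixed at zero, but it would affect a comparison of all TEAEs.

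**The case against.** The strongest reply is that this is a descriptive safety study. No hypothesis test is stated for adverse events, enrollment was set on practical grounds, and Section 8.4.3 already tabulates all TEAEs, SAEs and TEAEs by severity by group. Hospital admissions, all cause and COVID-19-related, are also summarized by group. On this view the control contributes to the safety evaluation as a whole, and only the label on one measure is awkward.

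Much of this stands. A reader might infer that the trial will have no comparative safety data; the planned tables show otherwise. A reader might also treat the lack of a stated between-group estimate or interval for adverse events as an omission. Section 8 leaves statistical detail to the SAP, which is not at hand, so that is no finding.

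What remains is the pairing of objective and endpoint, which the protocol itself fixes. An SAP could add an interval for the difference in SP-related TEAEs, but that difference would be no more informative. Description also needs a quantity that bears on the stated comparison.

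A second reply is that comparing all TEAEs does not escape open-label judgement. Section 7.3.3 keeps COVID-19 symptoms within expected progression out of the TEAE count, so the same diarrhea could be recorded as disease in one arm and as an adverse event in the other. This is correct and limits the remedy, most of all for GI events. It does not rescue the present endpoint, which depends on the same recording decision and adds a causality judgement to it.

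**Conclusion.** The concern holds for the primary endpoint. The objective compares two groups, and the sole endpoint can be validly counted in only one. The primary result will be a one-arm, investigator-attributed rate that cannot show excess risk over SSC. This follows from the protocol text and rests on no numerical assumption.

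A reader might also infer that Table 4 is wrong or overstates the trial's precision. It does neither: all eight rows are correct for a single rate, and the table claims no comparative precision. With SSC at zero, the one-arm Wald half-width is also the Wald half-width of the difference. The wider figures of 6.8 to 11.2 points (148 per group) and 6.4 to 10.4 points (170 per group) belong to a different endpoint, any TEAE, at equal rates that are assumed. The protocol gives no all-TEAE rate.

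**What to change.** - **Primary comparison.** Use the proportion of patients with any TEAE regardless of relatedness, with SAEs and GI TEAEs as supportive measures. Report the SSC + KB109 minus SSC risk difference with a 95% CI, adjusted for age group and comorbidity status. Site/center is also a stratification factor (Section 6.10), so include it or state that it is left out.
- **Start point.** Count TEAEs from the same point in both arms, for example Day 1, the morning after the study kit arrives. Both arms receive the kit.
- **SP-related TEAEs.** Keep them as a descriptive measure for the KB109 arm.
- **Table 4.** It may stay, labelled as one-arm precision. If two-arm precision is added for all TEAEs, use the half-widths above and state the equal-rate assumption.
- **Limitation.** Acknowledge that open-label reporting may affect whether GI symptoms are recorded as TEAEs or as COVID-19 symptoms.

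The cost is wording in the synopsis and Sections 3.2.1, 8.1 and 8.4.3. No new data are needed: adverse events are already collected from consent, all TEAEs are already tabulated by group, and Section 8.4.3 already reports group differences with 95% CIs for the symptom scores. The downside is a less favourable stated precision.

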### 3.2.2 Secondary Endpoints

The secondary endpoints are as follows:

- Time to resolution of overall 13 COVID-19 related symptoms which is defined as from Day 1 until the day at which the overall composite score of 13 COVID-19 related symptoms becomes 0 or 1 and remains at 0 or 1 for the rest of the Intake Period and for the Follow-up Period. Overall composite score of 13 COVID-19 related symptoms is the sum of 13 COVID-19 related symptom scores (i.e., cough, chills/repeated shaking with chills, muscle pain, fever, headache, anosmia/ageusia, shortness of breath, sore throat, gastrointestinal disturbance/symptoms, diarrhea, fatigue, nasal congestion, and chest tightness (CDC 2020). Each COVID-19 symptom will be recorded by patients on a scale of 0: Absent, 1: Mild, 2: Moderately severe, 3: Very severe. The overall composite score ranges from 0 (no symptoms) to 39 (very severe)
- Time to resolution of overall 8 cardinal COVID-19 related symptoms which is defined as from Day 1 until the day at which the overall composite score of 8 cardinal COVID-19 related symptoms becomes 0 or 1 and remains at 0 or 1 for the rest of the Intake Period and for the Follow-up Period. Overall composite score of 8 cardinal COVID-19 related symptoms is the sum of 8 cardinal COVID-19 related symptom scores (i.e., cough, chills/repeated shaking with chills, muscle pain, fever, headache, anosmia/ageusia, shortness of breath, and sore throat)
- Proportion of patients with reduction from Baseline (symptom present at Baseline) in each of 13 individual COVID-19 related symptom at EOI and Follow-up
- Proportion of patients with symptom becomes absent (symptom present at Baseline) at EOI and Follow-up for each of 13 individual COVID-19 related symptom
- Change from Baseline to EOI in overall composite score of 13 COVID-19 related symptoms
- Change from Baseline to EOI in overall composite score of 8 cardinal COVID-19 related symptoms
- Time to resolution of fever (defined as from Day 1 until the day at which a patient's daily maximum temperature achieves and remains below 100.4 °F for the rest of the Intake Period and for the Follow-up Period without an antipyretic medication)
- Proportion of patients with oxygen saturation <95% on Day 14 and Day 35

- Proportion of patients with oxygen saturation <98% on Day 14 and Day 35
- Measures collected from the Healthcare Provider Wellness Visits
- Proportion of patients experiencing hospital admissions during the Intake Period and Follow-up Period (all cause, and COVID-19-related)
- Healthcare Utilizations during the Intake Period and Follow-up Period

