## Part 2, Follow-up Period

On Day 15, all patients will enter the Follow-up Period (Days 15 to 35) where COVID-19 signs, symptoms and healthcare utilization indices will be collected weekly in TrialPace™ where appropriate. On Day 14, the Investigator will instruct the patients to stop the intake and return the SP during the Follow-up Period (Days 15 to 35). In addition, wellness visits by telephone call will be conducted on Days 21, 28, and 35 to follow-up on the patient's health status.

On Day 35, all patients will undergo another telemedicine visit where the following will be conducted: an abbreviated physical examination, an assessment of safety and other protocol-specified measures of health, and an evaluation of whether follow-up treatment is recommended. When wellness and telemedicine visits fall on the same day, they will be combined as a telemedicine visit. If feasible blood samples for clinical chemistries, biomarkers and serological measures of immunity, and nasal/oropharyngeal swabs for quantitative viral load assessments (research purposes only) will be collected; sample collection may occur at the patient's home by a healthcare professional, remotely, or at the study site or clinic.

For convenience, standard terms language included in International Conference for Harmonization (ICH) guidance relevant to the conduct of clinical trials are used in this protocol. An example of such a term used in this protocol is "treatment emergent," included in ICH E9. Use of this standard term is not intended to connote treatment with a medicinal product administered (ICH E9 2018).

Throughout the study, safety will be monitored by TEAEs, clinical signs and symptoms, and selected vital signs (i.e., temperature and oxygen saturation). Concomitant medications/supplements will be recorded throughout the study. Any patient experiencing a TEAE, or intolerable GI symptoms will be evaluated by the principal investigator (PI) or telemedicine provider for possible interruption and/or down-titration of SP dose to the previously tolerated level in consultation with the medical monitor.

In the event of significant worsening of COVID-related symptoms or two sequential pulse oximetry readings of <94% within 2 minutes, patients will be instructed to seek medical attention immediately (see [Section 6.7](#)).

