#### **4.3.7 Healthcare Utilization**

From Day 2 onwards, patient-assessed measures of healthcare utilization will be performed every morning upon waking until the end of the study (Intake Period plus Follow-up Period) (Table 1).

Measures will include:

- Prescription Medication Use – recorded as reason, type, dose and frequency
- Over-the-counter Medication Use – recorded as reason, type, dose and frequency
- Supplement Use – recorded as reason, type, dose and frequency
- Emergency room or Urgent Care visit – Rated as Y/N; if Y then reason will be recorded
- Medical provider visit – Rated as Y/N; if Y then reason as well as if this is a visit for a co-existing condition (mental health visit, physical therapy, etc.) will be recorded;
- Hospital stay – Rated as Y/N; if Y then reason will be recorded

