### **5 STUDY POPULATION**

#### **5.1 Inclusion Criteria**

To be considered for enrollment into this study, each patient must meet **all** of the following Inclusion Criteria:

1. Be male or female,  $\geq 18$  years of age
2. Be willing and able to give informed consent, and provide medical history, and secondary contact information
3. If symptomatic at the time of COVID-19 testing, the extended symptom(s), 8 cardinal plus additional 5 symptom(s) (see [Section 4.3.4.1](#) for reference) must be new or worsening at baseline and must not have been present (see [Section 4.3.4.1](#) for reference) for more than 5 days. Symptomatic patients must be screened and randomized within 48 hours of a positive test.
4. If pre-symptomatic at time of COVID-19 testing, new cardinal symptoms (see [Section 4.3.4.1](#) for reference) must be reported within 7 days of a positive test, and the patient must be screened and randomized within 5 days of them developing symptoms

5. Mild to moderate COVID-19 and self-reported outpatient management indicated by their healthcare provider
6. Able to adhere to the study visit schedule and other protocol requirements
7. Has consistent internet or cellphone access with a data plan, and access to a smartphone, tablet or computer

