### 8.3.2 Full Analysis Set

The Full Analysis Set will include all randomized patients and have both Baseline and at least one post-Baseline endpoint observation during intake period. Patients will be analyzed in the group to which they were randomized.

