#### Time to resolution of fever

The Kaplan-Meier method will be used to estimate median time to resolution of fever and resolution rate specific to each group. Kaplan-Meier graphs will be generated; quartiles and point probabilities will be calculated. Interval estimates will be calculated using 95% point-wise CIs.

Proportion of patients with oxygen saturation <95% (or <98%) on Day 14 and Day 35, and proportion of patients experiencing hospital admissions during the Intake Period and Follow-up Period will be summarized by group using frequencies and percentages.

Measures collected from the Healthcare Provider Wellness Visits and Healthcare Utilizations during the Intake Period and Follow-up Period will be summarized by group based on the Safety Analysis Set using the following descriptive statistics: sample size, mean, standard deviation, median, minimum value, and maximum value or using frequencies and percentages.

Further details of the model specification, assumptions, and SAS implementation codes will be provided in the SAP.

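### Time to resolution of symptoms and of fever is estimated in the whole Full Analysis Set, including patients with nothing to resolve at the start, which can only shorten the Kaplan-Meier medians

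*Protocol*

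**What the plan says.** **Endpoint definitions (Protocol 3.2.2).** The 13-symptom clock starts on Day 1 and runs "until the day at which the overall composite score of 13 COVID-19 related symptoms becomes 0 or 1 and remains at 0 or 1", a state that must last to the end of Intake and through Follow-up. The 8-symptom endpoint has the same form. Fever resolves when the "daily maximum temperature achieves and remains below 100.4 °F for the rest of the Intake Period" and through Follow-up, without an antipyretic. None of the three asks for a starting score or a starting fever.

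**Population and method (8.3.2, 8.4.3).** "The analysis of the following endpoints will be based on the Full Analysis Set unless otherwise specified". That set is "all randomized patients and have both Baseline and at least one post-Baseline endpoint observation during intake period". For fever, "The Kaplan-Meier method will be used to estimate median time to resolution of fever and resolution rate specific to each group"; the two composites get the same treatment, with quartiles and point probabilities as well.

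**Entry (5.1).** For patients symptomatic at testing, the symptoms "must be new or worsening at baseline and must not have been present" for more than 5 days. Any of the 13 symptoms will do. Patients pre-symptomatic at testing need new cardinal symptoms. Neither route sets a severity floor or requires fever. Section 4.3.4.1 scores a mild symptom as 1.

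**Contrast within 3.2.2.** The two individual-symptom proportions are confined to patients who had that symptom at Baseline.

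**Reading frequency in Days 15-35.** Section 4.1 describes a Follow-up Period "where COVID-19 signs, symptoms and healthcare utilization indices will be collected weekly in TrialPace". Section 4.3.7 says healthcare utilization is "performed every morning upon waking until the end of the study (Intake Period plus Follow-up Period"). Section 4.3.4.2 has signs taken daily and according to the schedule in Table 1.

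**The concern.** A time-to-resolution analysis describes patients who have something to resolve. Here the event can be met at the origin of the clock. One mild symptom gives a composite of 1, which already satisfies the threshold. A symptomatic entrant with only fatigue or nasal congestion scores 0 on the 8-symptom composite. A patient who never had fever is below 100.4 °F from the first reading.

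The start of the clock adds to this. Day 1 is the morning after the kit arrives, so it follows randomization and overnight shipping (4.1). The bar on recent significant improvement in Table 1, footnote 2, ends at randomization.

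At stake are the medians for three secondary endpoints and for the planned subgroup analyses of the two composites (8.4.4). The study title promises a natural history of the illness, so the absolute medians matter, as well as the contrast between groups. If the share with an immediate event is similar in both groups, any true difference in medians shrinks too.

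The frequency of later readings is a second, separate question. All three endpoints need resolution to hold through Day 35, and fever needs a daily maximum.

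**Working it through.** **The plan's own figures.** The protocol gives no expected median, event count or power for these endpoints, so there is nothing of that kind to reproduce. Its evaluable numbers do reproduce: 175 × 0.85 = 148.75, taken as 148, and 200 × 0.85 = 170 per group. They do not bear on this point.

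**Step 1: direction.** Let f be the share of the Full Analysis Set with the event on Day 1, and S1(t) the survival curve of the others. The analysed curve is S(t) = (1 − f) × S1(t). This is never above S1(t), so its median is never later than the at-risk median. No distributional assumption is needed.

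**Step 2: size, as an illustration.** Assume S1(t) = 2^(−t/m), an exponential curve with at-risk median m. Setting (1 − f) × 2^(−t/m) = 0.5 gives t = m × (1 + log2(1 − f)). Neither f nor m is in the protocol, so both are assumptions.

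| f | 1 + log2(1 − f) | Median, m = 10 | Median, m = 14 |
|---|---|---|---|
| 5% | 0.93 | 9.3 | 13.0 |
| 10% | 0.85 | 8.5 | 11.9 |
| 20% | 0.68 | 6.8 | 9.5 |
| 30% | 0.49 | 4.9 | 6.8 |
| 40% | 0.26 | 2.6 | 3.7 |
| 50% or more | 0 | Day 1 | Day 1 |

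With the same f in both groups, a difference in medians is multiplied by the factor in the second column.

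**Step 3: reading frequency.** The statements, side by side:
- Section 4.1: signs, symptoms and utilization are weekly in Follow-up.
- Table 1, symptom row: one Daily entry, with no separate marks at Days 14, 21, 28 or 35. The utilization row has the same layout, and 4.3.7 describes utilization as daily to the end of the study. Read alike, symptoms are daily to Day 35.
- Table 1, signs row: marks at Days 14, 21, 28 and 35, which fits weekly temperature. Section 4.3.4.2 says daily, and footnote 7 places signs inside the symptom row as well.

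The protocol therefore contradicts itself. Weekly has better support for temperature than for symptoms.

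**Step 4: consequence if readings are weekly.** With readings on Days 21, 28 and 35 only, a resolution in Days 15-35 is recorded 6, 5, 4, 3, 2, 1 or 0 days late, on average 21/7 = 3.0 days. A median on Day 16 is recorded as Day 21. In simulation, at-risk medians of 7, 10 and 12 days did not move. Quartiles are more exposed: under the same exponential curve the upper quartile is 2m, so any m above 7 days puts it after Day 14. With m = 8 it falls on Day 16 and is recorded as Day 21; with m = 10, Day 20 becomes Day 21.

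**The case against.** **Meeting the threshold on Day 1 is not enough.** The score must stay at 0 or 1, and entrants have recent symptoms that may worsen. The fever endpoint also requires no antipyretic, which Section 6.7 permits for symptom relief. This stands: the share at or below the threshold on Day 1 is an upper bound for f.

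**The SAP could add a restriction.** Section 8.4.3 leaves further specification to it. This carries limited weight. Section 8.4 says that it describes the methods for the primary and secondary objectives, and the definitions and population are stated in the protocol. A later restriction would change them.

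**A restriction has its own faults.** It drops patients who worsen only after Baseline. If based on Day 1 self-report in an open-label trial, it selects on a record made after allocation. Admitting anyone who took an antipyretic would bring never-febrile patients back into the fever set. All of this stands and shapes the fix.

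**The endpoints are secondary.** Section 8.4.3 plans no between-group test of them, and a Day 1 drop would be visible on the curves. This stands and limits the severity.

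**A stronger reading is tempting.** A reader might infer from Section 4.1 that all three endpoints rest on weekly readings after Day 14, so that the medians are wrong in both directions. The documents do not support that. Weekly is one side of a contradiction, and for the composites Table 1 points to daily. Late dating moves a median only if it falls after Day 14. The other possible effect of weekly readings, missed short relapses, makes resolution look earlier.

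**Conclusion.** The at-risk defect holds. As written, patients without the condition at the start enter all three analyses, and those who stay clear have the event on Day 1. The direction, towards shorter medians, is certain. The size is not: the figures of 8.5, 6.8 and 2.6 days rest on an assumed exponential curve, an assumed at-risk median of 10 days and assumed shares of 10%, 20% and 40%. Fever is the most exposed because entry does not require it; if half or more of the set had the event on Day 1, the fever median would be Day 1 and carry no information.

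On reading frequency, the documents support a contradiction to be reconciled, and late dating of medians or upper quartiles after Day 14 if readings prove to be weekly.

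This should be fixed, but it does not threaten the trial's main conclusion. The primary endpoint, study-product-related adverse events, and the precision-based sample size are unaffected.

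**What to change.** 1. In 3.2.2 and 8.4.3, limit each time-to-resolution analysis to patients with the condition at Baseline. For each composite, require that composite to be 2 or more. For fever, require a temperature of 100.4 °F or above or a fever symptom score of 1 or more; antipyretic use alone should not qualify.
2. Decide membership from screening diary entries made before randomization where they exist, otherwise from the pre-dose Day 1 record. Table 1, footnote 5, has the thermometer arriving with the kit, so before randomization the fever symptom score may often be the only record. State this rule separately from the averaged Baseline that 8.4.3 uses for the change scores. A patient who qualifies before randomization and has cleared by Day 1 would still have a Day 1 event, but a real one.
3. Keep the whole-set analysis as supportive.
4. Reconcile the Follow-up text in 4.1 with Table 1, 4.3.4.2 and 4.3.7. If readings are weekly, analyse resolutions after Day 14 as interval-censored, and say how a daily maximum temperature is to be judged.

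The cost is mainly wording. The analysed sets become smaller, chiefly for fever, and patients who worsen only after Baseline leave the main analysis. If the reconciled schedule is daily, more diary prompts may be needed in Days 15-35.
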